
### 4.5. Trial Participants/Sample Size

The target sample size to be recruited is based on change in the primary outcome measure of body mass in the SCI group. Effect size was calculated based on statistical guidelines established by Cohen [38], similar SCI-related body mass reduction interventions [39], and ES in terms of relative risk reduction for the DPP [29]. Given a significant moderate ES of 0.48, for a two-tailed Fisher’s least significant difference test based on the difference between pre- and post-TLI body mass, with an α = 0.05 and power of 1-β ≥ 0.90, we calculated sample size (N) would require N ≥ 24 per group.

We targeted the enrollment of 30 dyadic couples (30 SCI; 30 caregivers = 60) who satisfy the inclusion and exclusion criteria (outlined below). We assumed an attrition of 20%, yielding an analytic sample size of 48. We note that preliminary data specific to this type of multi-modal and comprehensive TLI in SCI are not available for a direct calculation of ES. It is important to note that power analyses are estimates and assumptions about the effect sizes, and other parameters can vary. Additionally, other factors such as variability in participant characteristics, study design, and protocols can influence statistical power. In this study, we maintain alignment with standard statistical practice and fidelity to the DPP primary trial outcome, body mass, measured before and after the clinical intervention and extension phase.

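### The stated N of 24 for 90% power does not follow from the stated inputs without an unstated effect-size definition or correlation, and the analytic size of 48 is not the size for the SCI-only primary outcome

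*Protocol article*

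**What the plan says.** All the sizing statements are in section 4.5 (Trial Participants/Sample Size) of the protocol article.

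- Basis: "The target sample size to be recruited is based on change in the primary outcome measure of body mass in the SCI group".
- Effect size: "Given a significant moderate ES of 0.48". It is attributed to Cohen's guidelines, similar SCI weight-loss studies and the DPP. The section adds that no preliminary data allowed a direct calculation. It gives no SD, no pre-post correlation and no name for the type of effect size.
- Test: a two-tailed Fisher "least significant difference test based on the difference between pre- and post-TLI body mass", "with an α = 0.05 and power of 1-β ≥ 0.90".
- Result: "we calculated sample size (N) would require N ≥ 24 per group".
- Enrolment: 30 dyads, that is 30 SCI participants and 30 caregivers, 60 people in all.
- Retention: "We assumed an attrition of 20%, yielding an analytic sample size of 48".

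Two other sections fix the structure. Section 4.1 describes a within-subjects repeated-measures design in which participants are their own controls. Section 4.4 says that every SCI participant receives the TLI and that only caregivers are randomized. The primary pre-post contrast therefore has a single SCI group.

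**The concern.** A pre-to-post contrast in one cohort at two time points is a paired t test. For a paired test at 0.48 with these error rates, 24 is about half the number one would expect. The section also opens by sizing on the SCI group and closes with an analytic total that includes caregivers, whose body mass does not enter that outcome. A reader who takes 48 as the size of the primary analysis would think it twice as large as it is.

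What is at stake is how the primary result is read. The article claims at most a 10% chance of missing its assumed effect. If that chance is in fact much larger, an inconclusive result would be taken as stronger evidence of no effect than it is. There is also a risk that the 0.90 is carried over to the only randomized comparison, complementary caregiver curriculum (CCC) versus control, for which the section makes no calculation.

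**Working it through.** **Inputs (section 4.5):** effect size 0.48; two-sided α = 0.05; target power 0.90; 30 SCI participants enrolled; 20% attrition.

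**Step 1. Head counts.** 30 × 0.8 = 24 SCI completers. 60 × 0.8 = 48 people, that is 24 SCI participants plus 24 caregivers. The 48 is reproduced as a count of people, not as the SCI analysis set.

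**Step 2. The plan's N, with 0.48 read as the standardized mean difference of the pairs (dz).** The normal approximation is n = ((1.960 + 1.2816)/0.48)² = 45.6, so 46. The exact power uses the noncentral t with n − 1 degrees of freedom and noncentrality 0.48·√n. At n = 24 the noncentrality is 0.48 × 4.899 = 2.35 against a critical value of 2.069.

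| SCI completers | Power at dz = 0.48 |
|---|---|
| 24 | 0.615 |
| 30 (no attrition) | 0.72 |
| 47 | 0.896 |
| 48 | 0.903 |

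The stated 24 is not reproduced; the exact requirement is 48. A one-sided test does not rescue it either: power at 24 is 0.738, and 39 are needed for 90%.

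**Step 3. What 24 completers can detect.** Solving the same power function at n = 24 gives dz ≈ 0.69 for 90% power and dz ≈ 0.60 for 80%.

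**Step 4. Readings that do return 24.** Two were found, and the article states neither.

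(a) 0.48 is scaled to the cross-sectional SD of body mass. With equal SDs before and after, and pre-post correlation ρ, dz = 0.48/√(2(1 − ρ)). The article gives no ρ, so a range is shown.

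| Assumed ρ | dz | Power at n = 24 |
|---|---|---|
| 0.5 | 0.48 | 0.615 |
| 0.7 | 0.62 | 0.83 |
| 0.76 | 0.69 | 0.90 |
| 0.8 | 0.76 | 0.945 |
| 0.9 | 1.07 | 0.999 |

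The break-even is ρ = 1 − ½(0.48/0.691)² ≈ 0.76.

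(b) 0.48 is Cohen's f with pre and post treated as two independent groups, so d = 2 × 0.48 = 0.96. Then 24 per group gives 0.902. This conflicts with the within-subject design and fits poorly with an effect called moderate.

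**Step 5. Could the groups be the two caregiver arms?** Thirty dyads in two equal arms is 15 per arm, and 15 × 0.8 = 12 evaluable, not 24. An independent two-sample t test at d = 0.48 has power 0.20 with 12 per arm and 0.37 even with 24 per arm. With 12 per arm, 80% power needs a difference of about 1.20 SD.

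**The case against.** The strongest reply is that 62% depends on a definition the article never gives. Section 4.5 attaches the pre-post difference to the test, not to the effect size, and does not say which SD the 0.48 is scaled to.

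The nutrition plan in section 6.1 gives this some force. It aims for a loss of about 7% of baseline body mass by week 24. If 7% is the assumed mean change and 0.48 is dz, the SD of change would be 7/0.48 ≈ 14.6% of body mass. Under normality about 32% of participants would then gain weight (standard normal probability below −0.48). Read on the baseline scale, the same division gives a between-person SD of about 14.6% of mean body mass, which sits more easily with the range of baseline weights in the diet plan (120 lb to over 250 lb). On that scale a high pre-post correlation would make 24 sufficient.

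This stands as a reason to treat 62% as conditional. It does not rescue the section as written, because neither the scale nor the correlation is stated and the claimed power depends on both. The section's general caution that power analyses are estimates does not close a twofold gap in N.

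Three stronger readings are tempting, and the document does not support them:

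- A reader might infer that the real chance of missing the effect is 38%. That holds only if 0.48 is dz.
- A reader might infer that the plan needed 48 and counted caregivers to get there. The article never states 48 as a requirement. Its stated requirement is 24, which 30 × 0.8 meets. The 48 in step 2 is a recalculation, and its match with the retained head count proves nothing about how the figure arose.
- A reader might infer that the article claims 90% power for CCC versus control. It does not: the sizing is expressly on the SCI group, and leaving a secondary comparison unpowered is not an error.

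**Conclusion.** The point holds in two parts.

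First, N of at least 24 with power of at least 0.90 does not follow from the inputs in section 4.5. On the plain reading (0.48 as the standardized mean of the paired difference) power at 24 SCI completers is about 62% and 48 completers are needed. On the cross-sectional SD scale, power at 24 is about 0.62 at a correlation of 0.5, reaches 0.90 at about 0.76 and exceeds 0.99 at 0.9. The document does not allow a choice between these, so the defect is a power claim resting on an unstated assumption, not a demonstrated power of 62%.

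Second, and whatever the effect-size scale, 48 is the wrong analytic size for the primary outcome. That outcome has 24 SCI completers; the other 24 people are caregivers.

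The figures assume a paired t test on SCI completers, exactly 20% attrition among SCI participants and, for the correlation range, equal SDs before and after. This is an error among stated figures, not a detail left to a fuller document: the inputs, the N and the power are all given and do not agree without an addition.

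**What to change.** Revise section 4.5 as follows.

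1. Give the analytic size for the primary outcome as 24 SCI completers of 30 enrolled, and label 48 as total people retained (24 SCI participants and 24 caregivers).
2. Then do one of two things. Either name the effect-size scale and state, with its source, the SD or pre-post correlation that supports 0.90 at 24. Or, if 0.48 is the standardized mean of the paired difference, restate the power as about 62% at 0.48, with 90% power at about 0.69.
3. Replace the phrase about N per group with wording that says which group is meant, since the primary contrast has one.
4. Add that the stated power does not apply to CCC versus control (about 12 versus 12 dyads), which will be reported as an estimate with a confidence interval.

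The cost is wording only. No participants, visits or measurements are added. Under the second option in item 2 a published figure becomes less favourable. Keeping 90% power at dz = 0.48 would instead mean enrolling 48/0.8 = 60 SCI participants, twice the plan; the correction does not require this.

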#### Eligibility Criteria

**Inclusion Criteria:**

**Criteria**

**Description**
Male and Female with SCI/D > 1 year, aged 18–65 years.Individuals of both sex with spinal cord injury/dysfunction (SCI/D) for more than one year, aged between 18 and 70 years.ASIA Impairment scale (AIS) A-C Spinal Cord Levels C5-L1Individuals with AIS scale ranging from A to D and spinal cord levels C5-L1Anyone or more of the following:Participants must meet at least one of the following criteria:a. Waist circumference >94 cm (37 inches)Waist circumference exceeding 94 cm (37 inches).b. BMI ≥ 22 kg/m^2^ [40,41]Body Mass Index (BMI) equal to or greater than 22 kg/m^2^.c. Fasting dyslipidemia (HDL-C≤ 40 mg/dL (male)/≤50 mg/dL (female), OR; TG ≥ 150 mg/dL)Presence of fasting dyslipidemia, indicated by HDL-C ≤ 40 mg/dL (males) or ≤50 mg/dL (females), or TG ≥ 150 mg/dL.d. Linked with caregivers: male and female 18–70 years who consent to co-enroll in the study as partnersCaregivers aged between 18 and 70 years, of both sex, who are willing to participate alongside the study participant and provide social and/or physical support. Caregivers include family members, significant others, or friends living with a disabled (SCI) partner and offering personal assistance, routine emotional encouragement, and/or social interaction.

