## Abstract

Background: Chronic spinal cord injury (SCI) significantly accelerates morbidity and mortality, partly due to the increased risk of cardiometabolic diseases (CMD), including neurogenic obesity, dyslipidemia, and impaired glucose metabolism. While exercise and dietary interventions have shown some transient benefits in reducing CMD risk, they often fail to improve clinically relevant disease markers and cardiovascular events. Moreover, SCI also places caregiving demands on their caregivers, who themselves experience health and functional decline. This underscores the need for more substantial interventions that incorporate appropriate physical activity, heart-healthy nutrition, and behavioral support tailored to the SCI population. Objectives: This randomized clinical trial (RCT) protocol will (1) assess the health and functional effects, user acceptance, and satisfaction of a 6-month comprehensive therapeutic lifestyle intervention (TLI) adapted from the National Diabetes Prevention Program (DPP) for individuals with chronic SCI and (2) examine the impact of a complementary caregiver program on the health and function of SCI caregivers and evaluate user acceptance and satisfaction. Caregivers (linked with their partners) will be randomized to ‘behavioral support’ or ‘control condition’. Methods: Dyadic couples comprise individuals with SCI (18–65 years, >1-year post-injury, ASIA Impairment Scale A-C, injury levels C5-L1) and non-disabled SCI caregivers (18–65 years). Both groups undergo lock-step circuit resistance training, a calorie-restricted Mediterranean-style diet, and 16 educational sessions focused on diet/exercise goals, self-monitoring, psychological and social challenges, cognitive behavioral therapy, and motivational interviewing. The outcome measures encompass the cardiometabolic risks, cardiorespiratory fitness, inflammatory stress, multidimensional function, pain, life quality, independence, self-efficacy, program acceptance, and life satisfaction for SCI participants. The caregiver outcomes include multidimensional function, pain, quality of life, independence, and perceived caregiver burden. Discussion/Conclusions: This study evaluates the effects and durability of a structured, multi-modal intervention on health and function. The results and intervention material will be disseminated to professionals and consumers for broader implementation. Trial Registration: ClinicalTrials.gov, ID: NCT02853149 Registered 2 August 2016.

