**Exclusion Criteria:**

For participants with SCI:
**Criteria****Description**Participating in at least 30 min of moderate-intensity physical activity for at least three months.Individuals engaged in moderate-intensity physical activity for a minimum of 30 min on at least three days per week for three months.Nutrition involving moderate caloric restriction for at least 6 months resulting in weight loss/gain ≥ 10% of total body massIndividuals who have undergone moderate caloric restriction resulting in a weight loss or gain of 10% of their total body mass over a period of at least 6 months.Surgery within 3 monthsIndividuals who have undergone surgery within the past three months.Grade 3–4 pressure ulcer within 3 monthsIndividuals who have had grade 3–4 pressure ulcers within the past three months.Limb pain that limits exerciseIndividuals experiencing limb pain that restricts their ability to exercise.Recurrent acute infection or illnessIndividuals with a history of recurrent acute infection or illness.PregnancyPregnant individuals.Previous myocardial infarction (MI) or cardiac surgeryIndividuals with a history of previous myocardial infarction (heart attack) or cardiac surgery.

For caregiver participants:
**Criteria****Description**Participating in at least 30 min of moderate-intensity physical activity for at least three months.Caregivers engaged in moderate-intensity physical activity for a minimum of 30 min on at least three days per week for three months.Nutrition involving moderate caloric restriction for at least 6 months resulting in weight loss/gain of 10% within the preceding 6 monthsCaregivers who have undergone moderate caloric restriction resulting in a weight loss or gain of 10% of their total body mass within the past six months.Surgery within 3 monthsCaregivers who have undergone surgery within the past three months.Limb pain that limits exerciseCaregivers experiencing limb pain that restricts their ability to exercise.PregnancyPregnant caregivers.Previous myocardial infarction (MI), cerebrovascular accident (CVA) or cardiac surgery that limits exerciseCaregivers with a history of previous myocardial infarction (heart attack), cerebrovascular accident (stroke), or cardiac surgery that limits their ability to exercise.Type I or II diabetes (by World Health Organization [WHO] criteria)Caregivers diagnosed with Type I or Type II diabetes according to World Health Organization (WHO) criteria.

Other exclusions applying to both groups:

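### The written inclusion rule requires no cardiometabolic risk criterion, because the linked caregiver is one of its alternatives, and the stated age and AIS limits conflict

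*Protocol article*

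**What the plan says.** The inclusion table in section 4.5 has a Criteria column and a Description column. After the age and injury rows comes a lettered list introduced by "Participants must meet at least one of the following criteria". Item a is a waist above 94 cm. Item b is "Body Mass Index (BMI) equal to or greater than 22 kg/m^2". Item c is fasting dyslipidemia. Item d is "Linked with caregivers: male and female 18–70 years who consent to co-enroll in the study".

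The SCI age row reads "Male and Female with SCI/D > 1 year, aged 18–65 years" in the Criteria column and "for more than one year, aged between 18 and 70 years" in the Description column. The injury row gives AIS A–C in the first column and A–D in the second. The Abstract describes the SCI participants as "18–65 years, >1-year post-injury, ASIA Impairment Scale A-C, injury levels C5-L1" and gives caregivers as 18–65, whereas both columns of the caregiver item say 18–70.

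Among the exclusions, the list for caregivers contains "Caregivers diagnosed with Type I or Type II diabetes according to World Health Organization (WHO) criteria". The list for SCI participants has no diabetes entry. The list that applies to both groups excludes pre-diabetes, and also any use of anti-hyperglycemic agents in the past six months.

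**The concern.** Section 4.4 rests the decision to give every SCI participant the lifestyle program partly on their raised cardiometabolic risk. Items a to c are the only inclusion criteria that would secure that risk, and an alternative that is always satisfied switches them off.

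The age and AIS rows are a different kind of fault. They are direct contradictions, and nothing in the article says which column prevails. A 68-year-old with SCI, or a candidate with AIS D, is eligible under one column and ineligible under the other.

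The trial is small, recruits at two centers and has no untreated SCI arm. The pre-to-post change in body mass therefore describes whoever was enrolled, and a reader needs to know who that was meant to be.

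**Working it through.** The article gives no figure to reproduce here. The check is to evaluate the rule as written and to compare the statements side by side.

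**The risk list.** Inputs: the at-least-one rule and items a–d (section 4.5); co-enrolment of SCI participants and caregivers as dyads (section 4.1); a target of 30 dyads (section 4.5).

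Rule as written: (a or b or c or d). Rule that fits the dyadic design: d and (a or b or c).

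| Candidate with SCI | As written | d and (a or b or c) |
|---|---|---|
| Waist 94 cm or less, BMI below 22, normal HDL-C and TG, with caregiver | passes | fails |
| BMI 22 or more, with caregiver | passes | passes |
| BMI 22 or more, no caregiver | passes | fails |
| None of a–c, no caregiver | fails | fails |

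For anyone enrolled as a dyad, d is true, so the written rule is true whatever the values of a, b and c. It also errs the other way: the third row passes the list without the partner that the design requires.

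**The limits.**

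| Limit | Abstract | Criteria column | Description column |
|---|---|---|---|
| SCI age | 18–65 | 18–65 | 18–70 |
| AIS grade | A–C | A–C | A–D |
| Caregiver age | 18–65 | 18–70 | 18–70 |

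The first two rows conflict inside the table. In the third the table agrees with itself and conflicts with the Abstract. Each age conflict is 70 − 65 = 5 years at the upper limit; the AIS conflict is one whole grade.

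**Diabetes.** For an SCI participant, pre-diabetes excludes. Diabetes treated with an anti-hyperglycemic agent in the past six months excludes through the drug criterion. Diabetes without such a drug in that period is not excluded by any listed criterion. HOMA2 and hemoglobin A1C are measured outcomes (section 5.1), so the gap bears on the glucose results.

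**Weight of one entrant.** With 30 SCI participants and the stated 20% attrition, 30 × 0.80 = 24 remain. One entrant is 1/24 = 4.2% of that sample. This is the weight of a single person, not an estimate of how many there will be. The article does not give the proportion of candidates failing all of a–c. The obesity prevalence in the Introduction, 55–95.7%, does not supply it: the remaining 4.3–45% are not obese, but some of them would still reach a BMI of 22 or meet item a or c.

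**The case against.** The strongest reply is that the intention is plain. Sections 4.1 and 4.5 make the dyad the unit of enrolment, the description of item d mainly defines who counts as a caregiver, and an either-or reading would admit SCI participants without a partner. Item d is then a requirement placed in the wrong list. That is probably what was meant. It does not rescue the text: the item carries its own letter in the a–d sequence, and the sentence governing the list asks for only one of them.

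A second reply is that the practical effect is small. BMI of 22 is a low bar, and a or c alone also suffices, so few candidates are likely to fail all three. This stands, and it limits the size of the point.

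A third is that this is a journal article, and the full protocol and screening forms may be correct. That is possible and cannot be checked here. But the fault is not an omitted detail: the article states the criteria and states them in conflict.

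On diabetes, the reply is that different exclusions for the two groups are not a contradiction. That is so, and it makes the point secondary. It remains odd that the milder state excludes an SCI participant while diabetes without recent drug treatment does not.

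**Conclusion.** The eligibility rules are wrong as written and need correcting. Under the stated rule, no dyad has to meet a cardiometabolic risk criterion. SCI age and AIS grade each have two incompatible limits within one row, and caregiver age differs between the Abstract and the table. The diabetes asymmetry is a lesser matter. The conclusion rests only on the wording and on universal dyadic enrolment.

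Several stronger readings are tempting, and the documents do not support them:

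- A reader might infer that every dyad is eligible. Item d disposes only of the risk step; age, time since injury, AIS, level and all exclusions still apply.
- A reader might infer that many participants without raised risk will enter, or that they will dilute the change in body mass. The number is unknown and probably small. The dietary energy deficit and the weight loss of about 7% in section 6.1 are not confined to people meeting a–c, and nothing in the article shows a smaller change in those who do not.
- A reader might infer that the two centers are applying different rules. The text would permit it, but the screening forms are not shown.
- A reader might take 18–65 and A–C as correct because the Abstract has them. The documents cannot settle which ranges are right.

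**What to change.** Take the linked caregiver out of the lettered list and make it a separate mandatory criterion. Then require at least one of a, b or c.

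State one SCI age range, one caregiver age range and one AIS range, identical in the Abstract and both table columns, according to what enrolment actually used.

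Reconcile the diabetes and pre-diabetes exclusions for SCI participants, so that the text shows whether diabetes without recent drug treatment is meant to be admitted.

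If the full protocol or the screening forms carry the same wording, they need the same correction. The cost is a change of wording and, depending on which ranges are kept, possibly a slightly smaller recruitment pool. Sample size and analysis do not change.
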